#### Management of excluded, withdrawn, and discontinued cases

Documentation and Follow-up: All withdrawals or discontinuations will be fully documented. A follow-up will be performed to identify the reason for discontinuation. All previously collected data will be retained for analysis;Data Handling: Participants completing less than 50% of scheduled interventions will be classified as major protocol violators. Their data will be excluded from per-protocol analysis but may be included in intention-to-treat analysis for sensitivity testing;Adverse Event Management: Participants discontinuing due to adverse events or insufficient response will receive timely clinical care or referral as needed;Post-Trial Care: If the study intervention is ineffective, alternative treatment options may be discussed with the participant within ethical guidelines;Sample Size Maintenance: If the dropout rate exceeds the pre-specified threshold, additional participants will be recruited to maintain statistical power.

#### Strategies to ensure participant compliance

Informed Consent: Participants will receive a detailed explanation of the protocol, potential risks, adverse events, and management strategies before providing written informed consent;Regular Communication: The research team will maintain consistent contact, address questions promptly, and support participants throughout the trial;Standardized Care: A comfortable treatment environment and consistent, high-quality intervention will be provided. All investigators and operators will complete standardized training;Adherence Monitoring: For the press-needle group, self-pressure and treatment completion will be recorded in diaries. For the naproxen sodium group, medication intake will be documented daily and verified via telephone follow-ups to ensure compliance.

Zusanli (ST36)	Stomach Meridian	On the anterior aspect of the leg, on the line connecting the depression lateral to the patellar ligament (ST35) with the lateral condyle of the tibia. 3 cun inferior to ST35, one finger-width (middle finger) lateral from the anterior crest of the tibia.	As the He-Sea point and Lower He-Sea point of the Stomach, it is a principal point for regulating the digestive system, strengthening Qi and Blood, and enhancing overall vitality. It is widely used to treat gastrointestinal disorders, fatigue, and to support recovery from chronic illnesses.
Taixi (KI3)	Kidney Meridian	On the medial aspect of the foot, in the depression between the prominence of the medial malleolus and the calcaneal tendon (Achilles tendon), level with the tip of the medial malleolus.	As the Yuan-Source point and Shu-Stream point of the Kidney Meridian, it is the most important point for nourishing Kidney Yin and Yang, replenishing Essence (Jing), and regulating water metabolism. It is indicated for weakness, low back pain, dizziness, tinnitus, and disorders of the reproductive and urinary systems.
Xuehai (SP10)	Spleen Meridian	On the medial aspect of the thigh, 2 cun proximal to the medial superior border of the patella (i.e., 2 cun above the medial patellar angle), on the bulge of the vastus medialis muscle.	Its name means “Sea of Blood.” As a key point on the Spleen Meridian, it regulates Blood circulation, cools Blood, and stops abnormal bleeding. It is the primary point for blood-related disorders such as irregular menstruation, dysmenorrhea, anemia, and skin conditions like eczema and urticaria (hives).

B-cun (Body-cun): The unit of measurement is the individual patient’s own proportional body cun. For limb measurements, the width of the patient’s interphalangeal joint of the thumb is defined as 1 B-cun. Location Verification: Final point location should be confirmed by gentle palpation to identify a tender spot or slight depression before needle application.

**Figure 2 fig2:**
[figure not shown]
Premenstrual phase acupoint diagram.

Postmenstrual phase (2 sessions, 2–3 days after menstruation ends): GB20 + Sanyinjiao (SP6), Zusanli (ST36), Taixi (KI3), to nourish liver and kidney, replenish blood, and regulate Chong and Ren meridians. Acupoint locations are detailed in Table 1 and Figure 3.

**Figure 3 fig3:**
[figure not shown]
Postmenstrual phase acupoint diagram.

### Preparation and disinfection

The acupuncturist will wash hands and wear disposable medical gloves. The target skin area will be disinfected with a 70–75% sterile alcohol swab in a centrifugal motion and allowed to air-dry for about 30 s.

### Needle insertion

A disposable sterile press needle (0.18 mm diameter, 1.3 mm length; Suzhou Global Acupuncture Medical Equipment Co., Ltd.) will be used. The needle will be perpendicularly and fully inserted into the skin at the target point with a gentle flicking motion, until the adhesive patch is firmly attached. No additional manipulation is needed.

### Needle retention

The needle will be retained for 48 h. Participants will perform standardized self-pressure and inspect the site daily for redness, swelling, pain, or accidental detachment.

### Removal and disposal

After 48 h, participants will remove the needle and patch before the next visit. Used needles and dressings will be disposed of in designated sharps containers following hospital biohazard protocols.

### Adverse event monitoring

Participants will immediately report persistent local pain, purulence, systemic fever, or complete needle loss. All such events will be documented as adverse events (AEs).

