### Safety outcomes

All adverse events (AEs) and serious adverse events (SAEs) were recorded from the time of signed informed consent until the 3-month follow-up after intervention. The occurrence time, symptoms, severity, duration, management, outcome, and causality with interventions were documented in detail.

Sequential press-needle group: Local skin reactions at the press-needle insertion sites were mainly monitored, including redness, itching, pain, rash, infection, and bleeding.

Oral naproxen sodium group: Adverse reactions related to NSAIDs were intensively monitored, including gastrointestinal reactions (nausea, stomachache, acid reflux, abdominal distension, gastrointestinal discomfort), neurological reactions (dizziness, headache, fatigue), skin allergy (rash, itching), and abnormal liver and renal function.

All systemic AEs were recorded in both groups. The incidence, severity, and causality of AEs were compared between groups to comprehensively evaluate the safety of the interventions.

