#### Exploratory and safety analyses

Exploratory Biomarkers/Imaging: Changes in serum biomarker levels (CGRP, estradiol, progesterone) and neuroimaging metrics will be analyzed using paired t-tests or Wilcoxon signed-rank tests within each group, and between-group comparisons will be made using ANCOVA. Correlation analyses (Pearson’s or Spearman’s) will explore relationships between clinical, autonomic, and biomarker/imaging changes. All exploratory findings will be reported with effect sizes and 95% CIs, and will be explicitly labeled as “exploratory, unadjusted for multiple comparisons, for hypothesis generation only” to prevent overinterpretation.

Safety Analyses: The incidence of adverse events (AEs) and serious adverse events (SAEs) will be summarized by treatment group, described by system organ class and preferred term. Differences in AE rates will be compared using Fisher’s exact test.

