#### Adverse event reporting and harms

All AEs occurring from the time of consent until the end of the study will be recorded, including description, severity, duration, action taken, causality assessment (related/unrelated to intervention), and outcome. SAEs will be reported to the PI and the IRB within 24 h of awareness. The PI will determine causality. An annual safety report will be submitted to the IRB. All AEs will be listed and summarized in the final publication.

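### Complete needle loss counts as an adverse event even without harm, so a device event possible in only one arm enters the AE comparison with naproxen

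*Protocol article*

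**What the plan says.** All places are in the protocol article.

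- *Adverse event monitoring* lists what press-needle participants must report at once and how it is classified: "Participants will immediately report persistent local pain, purulence, systemic fever, or complete needle loss. All such events will be documented as adverse events (AEs". Complete needle loss is on the list, with no condition of symptom or injury.
- *Needle retention* fixes 48 h of wear and asks participants to "inspect the site daily for redness, swelling, pain, or accidental detachment". Detachment is not classified here or elsewhere, and it is not related to complete needle loss.
- *Safety outcomes* describes the press-needle arm this way: "Local skin reactions at the press-needle insertion sites were mainly monitored, including redness, itching, pain, rash, infection, and bleeding". Needle loss is not named. The same section sets the overall scope: "All adverse events (AEs) and serious adverse events (SAEs) were recorded from the time of signed informed consent until the 3-month follow-up after intervention". It also says that incidence, severity and causality are compared between groups.
- *Adverse event reporting and harms* repeats the scope: "All AEs occurring from the time of consent until the end of the study will be recorded".
- *Exploratory and safety analyses* tabulates AEs by arm, system organ class and preferred term, and then states: "Differences in AE rates will be compared using Fisher’s exact test".
- *Treatment fidelity and environmental control* already documents needle retention time for the press-needle arm.

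**The concern.** A needle that falls off and does nothing to the skin is a failure of adhesion and a shortfall in treatment exposure, not a harm. Under the protocol it is nevertheless an AE, and nothing removes it from the rates that are tested. It has no counterpart on naproxen, so every participant whose only event is a needle loss adds to one side of the comparison. Daily inspection makes it likely that losses will be noticed.

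Safety and tolerability are stated aims in the Abstract and Objectives, and the Discussion argues for better tolerability than naproxen. The between-group AE comparison is the main evidence for that. Counting harmless losses works against the experimental arm. If the team instead decides whether to count them once the data are in, the choice is made in an open-label trial with the losses already known.

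**Working it through.** **The plan's own figure.** *Sample size* gives 30 evaluable participants per group and 20% dropout: 30 / 0.80 = 37.5, rounded up to 38 per group, 76 in total. This reproduces. The protocol states no AE rate and no needle-loss rate, so everything below on size rests on assumptions.

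**Inputs from the protocol**
- Sessions: 4 per cycle × 3 cycles = 12 (*Abstract*, Methods).
- Points per session: 4 in the premenstrual phase and 4 in the postmenstrual phase (*Acupoints and sequential regimen*). One or both sides is not stated.
- Placements per participant: 12 × 4 = 48, or 96 if bilateral.
- Test: Fisher's exact test, with the two-sided 0.05 level from *Statistical methods*.

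**Assumptions**
- Each needle is lost with probability p, independently of the others.
- All 12 sessions are delivered.
- Every loss counts as complete needle loss.
- 20% of participants in each arm have some other AE.
- A participant counts once, however many losses occur.

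**Formulas.** With m placements, the probability of at least one loss is L = 1 − (1 − p)^m. AE incidence including losses is 1 − (1 − 0.20)(1 − L), so the rise over 20% is 0.80 × L. The chance of p < 0.05 comes from exact enumeration at 38 versus 38, with the arms differing only by needle loss.

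| Loss per needle (assumed) | L, 48 / 96 placements | Rise in AE incidence, points | Chance of Fisher p < 0.05 |
|---|---|---|---|
| none counted | 0 | 0 | 2.7% |
| 0.1% | 4.7% / 9.2% | 3.8 / 7.3 | 4.0% / 7.5% |
| 0.5% | 21% / 38% | 17 / 31 | 30% / 75% |
| 1% | 38% / 62% | 31 / 50 | 75% / 99% |

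**Loss rate needed for a given shift.** A 10-point rise needs L = 0.10 / 0.80 = 0.125, which is p of about 0.28% with 48 placements or 0.14% with 96. A 20-point rise needs L = 0.25, which is about 0.60% or 0.30%.

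**Sensitivity to the base rate.** At 0.5% loss, the rise is 19 / 34 points with a 10% base and 15 / 27 points with a 30% base.

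**In participants.** With 8 of 38 having an AE on naproxen, 17 of 38 on press-needle gives p = 0.0497. Starting from 8 in each arm, 9 press-needle participants whose only event is a needle loss would be enough.

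**Sensitivity to clustering.** At 0.5% and 48 placements, 38 × 48 × 0.005 = 9.1 losses are expected. Independence spreads them over 0.214 × 38 = 8.1 participants. If each affected participant had two losses, about 9.1 / 2 = 4.6 would be affected and the shift would be a little over half as large.

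**The case against.** The strongest reply is that the sections, read together, give one answer. A reader might infer two conflicting definitions of an AE, one counting needle loss and only persistent pain, the other counting any pain and no needle loss. The text does not support that. *Adverse event monitoring* is an immediate-report list and does not say that lesser pain is not an AE. The list in *Safety outcomes* is open, introduced by words meaning mainly and including. Both *Safety outcomes* and *Adverse event reporting and harms* record all AEs. Complete needle loss is therefore counted consistently, and pain of any duration is captured.

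It can also be said that:

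- Tabulation by preferred term should make needle loss visible, so a reader could set it aside.
- Counting it does not flatter the new treatment.
- The trial is a pilot whose results are to be read descriptively (*Handling of multiple comparisons*), and no decision rule rests on the AE test.
- Details of AE coding are often left to a full protocol or analysis plan.

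Most of this stands, and it limits the consequence. It does not remove the point. The article does not leave the classification open: it makes harmless loss an AE. A preferred-term table shows how many participants lost a needle, but it need not show how many had nothing else, so the tested rate cannot be corrected from it.

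**Conclusion.** The concern holds in a limited form. As written, a device or exposure event that can occur in only one arm enters the between-group AE rate and biases it against press-needle. Whether accidental detachment enters as well is not settled.

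The size is conditional. Under the stated assumptions the rise runs from about 4 points (0.1% loss, 48 placements) to about 50 points (1%, 96 placements). A reader might take a shift of tens of percentage points to be a property of the plan. It is not: the protocol gives no loss rate, and at 0.1% the rise is only 4 to 7 points. Missed sessions, clustering, or a reading of complete loss that excludes ordinary detachment would all reduce it.

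A reader might also infer that at 1% loss and 48 placements about 15 of 38 participants (0.383 × 38 = 14.6) would have an AE and no harm. That figure is everyone with at least one loss. With a 20% base, those with a loss only number 0.383 × 0.80 × 38 = 11.6, about 12. Nor can it be said that the direction of the comparison would reverse, since no naproxen AE rate is given.

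The effect is confined to the descriptive safety and tolerability comparison.

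**What to change.** Reconcile *Needle retention*, *Adverse event monitoring*, *Safety outcomes* and *Exploratory and safety analyses* on these lines:

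1. Define complete needle loss and accidental detachment, or use one term for both.
2. Record either, when there is no injury, as a device or fidelity event alongside the needle retention time already kept under *Treatment fidelity and environmental control*. Immediate reporting by participants can stay.
3. Keep loss with injury or with a retained fragment as an AE.
4. State in *Exploratory and safety analyses* that device events without injury are excluded from the between-group AE rate and shown in their own row for the press-needle arm.

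The cost is wording in four sections, one extra case report form category and one table row. The AE incidence will no longer include device events, so the separate row must always be reported beside it. The change should be made before any outcome data are seen.

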### Standardized self-pressure protocol

Participants will be trained to press the center of the needle pad gently for 1 s per press, 12 repetitions per acupoint per session, 3 sessions daily. Compliance will be monitored via paper diaries, telephone follow-ups, and alarm reminders.

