### Compliance monitoring

Medication intake was recorded daily in a medication diary. Adherence was verified via telephone follow-up to ensure correct timing and dosage.

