### Treatment fidelity and environmental control

Treatment fidelity will be verified by random audit and standardized record review:

For the press-needle group: documentation of acupoint location, needle retention time, and immediate adverse events.

For the naproxen sodium group: verification of drug dosage, administration timing, and participant adherence. All procedures will be conducted in a quiet, dedicated, and consistent clinical environment to minimize external interference.

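### Alarm reminders are stated for the press-needle arm only, and telephone calls are described as verifying naproxen intake that they can only re-ask about

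*Protocol article*

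**What the plan says.** All references are to the protocol article.

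**Press-needle arm.** The section on the standardized self-pressure protocol states: "Compliance will be monitored via paper diaries, telephone follow-ups, and alarm reminders". The section on strategies to ensure compliance adds: "For the press-needle group, self-pressure and treatment completion will be recorded in diaries". Licensed acupuncturists place the needles (first Quality control section, under Interventions). Sessions are subject to random audit, with photographs of point location as an example (second Quality control section, Treatment Fidelity).

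**Naproxen arm.** The Compliance monitoring section states: "Medication intake was recorded daily in a medication diary" and then: "Adherence was verified via telephone follow-up to ensure correct timing and dosage". The section on strategies to ensure compliance repeats this: "For the naproxen sodium group, medication intake will be documented daily and verified via telephone follow-ups to ensure compliance". The Abstract names the same two methods. Pharmacists or nurses dispense the drug.

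**Both arms.** Under Treatment fidelity and environmental control: "Treatment fidelity will be verified by random audit and standardized record review". The naproxen item there reads: "For the naproxen sodium group: verification of drug dosage, administration timing, and participant adherence". Table 2 schedules a protocol compliance check at Months 1, 2 and 3. The daily reminders under Data collection and management belong to the electronic headache diary, not to treatment.

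**The concern.** The two compliance paragraphs are parallel. Each lists the methods for its own arm, and the lists differ by one item, the alarm. An alarm is more than a way of recording adherence, because it prompts the participant to act. Given to one arm only, it is a co-intervention in a trial where participants know their allocation and where the comparator has to be started on a predicted date and taken twice a day.

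The second issue is the claim that telephone contact verifies naproxen intake. The person on the telephone is the person who filled in the diary, so agreement between the two says little about tablets taken.

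Two uses of the data are affected. The trial's stated product is an effect-size estimate for planning a later confirmatory trial, so an avoidable handicap to the comparator would be carried into that plan. Treatment adherence is also named as an auxiliary variable in the multiple imputation of the primary outcome, where for naproxen it would rest on self-report.

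**Working it through.** The plan states no figure for adherence or its effect, so there is none to reproduce on this point. The only related design figure is the enrolment target, which reproduces: 30 / (1 − 0.20) = 37.5, rounded up to 38 per arm, and 2 × 38 = 76. It matters here only for costing the fix.

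**Step 1. Methods side by side.**
- Diary: both arms.
- Telephone follow-up: both arms.
- Alarm reminder for the treatment task: press-needle (self-pressure) only.
- Random audit and record review: both arms. For naproxen it names dosage, timing and adherence. For press-needle it names point location, retention time and immediate adverse events.
- Act carried out by staff: needle insertion in the press-needle arm. Staff dispense naproxen, but no intake is described as observed.
- Objective measure of naproxen intake: none stated.

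**Step 2. How much of each treatment is seen by staff.**
- Insertions: 4 sessions per cycle × 3 cycles = 12, all performed by staff.
- Self-pressure: 12 placements × 2 days × 3 sessions per day = 72 home sessions (taking the 48 h retention as two full days), none observed.
- Naproxen: 2 intakes per day × 5 to 7 days × 3 cycles = 30 to 42 home intakes (using the typical course length stated), none described as observed.

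Verification is therefore better for press-needle at the 12 insertions. It is of the same kind in both arms (diary plus telephone) for the 72 self-pressure sessions and the 30 to 42 intakes. Needle removal is also done by the participant.

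**Step 3. Direction.** Let E be the benefit of naproxen at full adherence, and d the fall in naproxen adherence that exists because that arm has no reminder. If benefit falls in proportion to doses missed, the naproxen mean loses d × E and the between-group contrast moves by that amount towards press-needle. The direction needs E > 0 and d > 0.

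**Step 4. Size.** The documents give neither E nor d, and no standard deviation for headache days. No value for the shift, absolute or relative to the standard error, can be derived from them.

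**The case against.** The strongest case on the other side has four parts.

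- **The alarms are narrow in scope.** They are described for self-pressure, a task repeated three times a day. They are not said to support attendance or needle retention. Naproxen is tied to breakfast and dinner, which are prompts in themselves, and nothing in the documents shows that the alarms open an adherence gap. This stands as a limit on size. It does not explain why one arm should have the device and the other not.
- **Naproxen is not checked by telephone alone.** A reader might infer that it is, and that verification as a whole favours press-needle. The text does not support either inference. There is also a daily medication diary, and the audit and record review names naproxen adherence. The home part of press-needle is as self-reported as the tablets, and staff insertion is inherent in comparing a practitioner-delivered treatment with a tablet. What remains is that the audit names no objective source and may only re-read the self-reports.
- **Tablet counting may be in the full protocol or a pharmacy manual.** This is fair, and the absence of a count from an article is not a defect in itself. The point rests on what the article does state, namely that calls verify timing and dosage.
- **The trial is exploratory.** Results will be read descriptively, the intention-to-treat population keeps everyone as randomized, and power for superiority or non-inferiority is disclaimed. This lowers the stakes. It does not protect an effect-size estimate that is meant to feed the next trial's sample size.

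A tablet count also measures adherence without restoring it. Only equal reminders address the imbalance in support.

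**Conclusion.** The point holds in a limited form and is a low-cost improvement, not a flaw that prevents the trial from running. As written, adherence support is unequal: treatment reminders go to one arm of an open-label comparison. Telephone contact is described as verification although it repeats self-report. The checking advantage for press-needle is confined to staff-delivered insertion and does not extend to self-pressure or needle retention.

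The contrast would move towards press-needle only if naproxen is effective and the missing reminders leave its adherence lower than it would otherwise be. Both conditions are assumptions. A reader might infer a material bias in the primary result, but the documents do not support that, since the size of any shift cannot be computed from them.

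**What to change.** 1. **Equal reminders.** In Compliance monitoring, and in the section on strategies to ensure compliance, state that the naproxen arm receives the same type of alarm reminder for its assigned intake as the press-needle arm receives for self-pressure. Nothing in the assigned regimen changes.
2. **A count in place of telephone verification.** In the same two sections, replace the statement that telephone calls verify intake with a count of returned tablets at the Month 1, 2 and 3 compliance checks in Table 2. Express it as tablets not returned over tablets due under the assigned regimen in that cycle. Keep the diary and report it beside the count, because a count shows neither timing nor whether a missing tablet was swallowed.
3. **Use in analysis.** Under Handling of missing data, name the count as the naproxen adherence measure in the imputation model. The per-protocol threshold is a separate matter: it is spelled out only in needle sessions, so the count cannot feed it until a naproxen criterion is written.

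**Cost.** A few sentences of protocol text, reminder set-up for 38 participants, and at most 38 × 3 = 114 counts of a few minutes each at checks already scheduled. No additional visit is needed. If the full protocol already has a count, one sentence in these sections pointing to it is enough for item 2.
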